### Follow-up

Both peri-procedural and mid-term clinical outcomes are included in the follow-up plan (Fig. 2). All patients will be followed for 12 months. Patients will receive a mail message and phone call 2 weeks in advance to remind them of the time point for following up. The SPIRIT (Standard Protocol Items: Recommendations for Interventional Trials) checklist is in presented in Additional file 2.

**Fig. 2 Fig2:**
[figure not shown]
Time schedule of the study. Abbreviation: *PPCI* primary percutaneous coronary intervention

### Outcomes

#### Primary endpoints

Since the study is focused on the optimal interventional strategy for patients with LM-AMI in order to reduce the mortality and incidence of adverse events, the primary endpoint is a composite of all-cause mortality or recurrent MI at 30 days after PPCI.

#### Secondary endpoints

Secondary endpoints include all-cause mortality, cardiac death, recurrent MI, and unplanned target vessel revascularization. The time frame and methods of data acquirement are shown in Table 2. All clinical events relating to endpoints are reported to and adjudicated by an independent clinical endpoints committee, which consists of five cardiologists not participating in this trial. The definitions of endpoints are clarified in Additional file 3: Table S2.

**Table 2 Tab2:** Time frame and data collection of primary and secondary outcomes

Endpoints	Composition	Time frame	Data collection
Primary endpoints	All-cause mortality or recurrent myocardial infarction (MI)	30 d	History
Secondary endpoints	All-cause mortality	30 d/6 m/1 y	History
	Cardiac death	30 d/6 m/1 y	History
	Recurrent MI	30 d/6 m/1 y	History
	Unplanned target vessel revascularization	30 d/6 m/1 y	History

### Data collection and management

Patients’ baseline characteristics are collected with case report forms (CRFs) during hospitalization at least 24 h after PPCI by investigators of each center. Angiographic data are recorded in the PCI procedure. According to the follow-up plan, patients are required to undergo recording of history and echocardiogram in each center at 1- and 12-month follow-up.

Data as outlined above will be collected with electronic CRFs by investigators and research coordinators and transferred to an encrypted online database operated by Zhongshan Hospital. The original CRFs and other records of data will be uploaded to the database. Data usage adheres to local laws and regulations of participating centers. Patient privacy is protected by restricting the access to dataset to relevant individuals—investigators, statistical analyzers, clinical research associates (CRAs), and representatives of the ethics committee—and replacement of the actual names in the documents with serial numbers. Representatives of participating centers are responsible for collecting data of enrolled patients in that center and uploading to the database. Angiographic and echocardiographic data are stored in CD-ROMs and sent to a core lab in Zhongshan Hospital, where the data are analyzed by specialists blinded to random allocation.

### Statistical analyses

Numerical data are summarized with means and standard deviations or medians with interquartile ranges depending on the distribution. Categorical data were described as proportions and percentages. Comparisons of numerical variables are conducted with the Student *t* test. Categorical variables and outcomes were compared by using the chi-squared test or Fisher exact test. All tests were two-tailed with a significant level of 0.05. Logistic regression is applied to adjust the significant variables in baseline data between the two groups and assess the outcomes presented with odds ratios and 95% confidence intervals. All data are analyzed by independent statisticians blinded to the random allocation using Stata version 14.0 and SAS version 9.4 (or higher versions of these programs).

The statistical analyses of primary and secondary outcomes will be conducted in both the intention-to-treat set and the per-protocol set. According to the intention-to-treat principle, all of these eligible patients who actually did not receive deferred stenting will still be included in the intention-to-treat analysis. In the per-protocol set, patients who undergo randomization but withdraw consent to participate or not treated according to the allocated procedure after randomization will be excluded from per-protocol statistical analyses.

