**Methods:**

The Optimal Strategy of Primary Percutaneous Coronary Intervention for Acute Myocardial Infarction due to Unprotected Left Main Coronary Artery Occlusion (OPTIMAL) study (ClinicalTrials.gov Identifier: NCT03282773) is an open-label, randomized, multicenter clinical trial in which 480 patients presenting with AMI caused by left main coronary artery occlusion recruited from 30 hospitals in mainland China will be randomly assigned 1:1 to immediate stenting or deferred stenting (scheduled 4–10 days after primary angioplasty) groups. The primary endpoint is a composite of all-cause mortality or recurrent myocardial infarction at 30 days after randomization. The secondary outcomes include all-cause mortality, cardiac death, recurrent myocardial infarction, and unplanned target vessel revascularization at 30 days, 6 months, and 12 months.

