### Sample size

The annual primary outcome event rate is 22.9%, which we estimated through integrating results of several observational trials [7, 22–26]. Because research data about stent implantation in patients with LM-AMI cannot be found, we have to use the data from other trials that enrolled only a few patients with LM-AMI. According to the results of the OPTIMAL study and the experience of our center, we determined a 35% relative decrease in primary outcome, which is conservative given the high mortality and incidence of adverse events for LM-AMI [15]. The study planned to enroll 240 patients for each arm given a 10% rate of loss (two-sided alpha of 0.05 and 80% power to demonstrate the relative decrease).

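### The 6- and 12-month secondary endpoints are compared only with fixed-time binary methods, which cannot use partial follow-up, although 10% loss is allowed for

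*Protocol article*

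**What the plan says.** All of this is in the protocol article.

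- **Test (Statistical analyses).** "Categorical variables and outcomes were compared by using the chi-squared test or Fisher exact test".
- **Adjusted analysis (same section).** Logistic regression is used to "assess the outcomes presented with odds ratios and 95% confidence intervals". No time-to-event method is named, and the section applies its analyses to primary and secondary outcomes alike.
- **Endpoints (Secondary endpoints, Table 2, abstract).** "Secondary endpoints include all-cause mortality, cardiac death, recurrent MI, and unplanned target vessel revascularization". The abstract sets all four, up to "unplanned target vessel revascularization at 30 days, 6 months, and 12 months", and Table 2 gives the same three times.
- **Follow-up.** "All patients will be followed for 12 months".
- **Loss (Sample size).** "The study planned to enroll 240 patients for each arm given a 10% rate of loss". The 10% is not tied to a time point.
- **Withdrawal (Ethical considerations).** For deferred-arm patients who withdraw between the first angiography and the second PCI, follow-up stops.
- **Analysis sets (Statistical analyses).** The intention-to-treat set keeps patients who did not receive deferred stenting. The article gives no rule for a patient whose 6- or 12-month status is unknown.

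**The concern.** Chi-squared, Fisher and logistic analyses need a yes or no for every patient at the chosen time. A patient last seen event-free at month 5 has no such value at month 6 or 12, and these methods have no place for the five event-free months. Two simple conventions are open:

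- **Drop the patient.** Early events stay in the numerator while event-free patients leave the denominator, so the risk is overstated.
- **Count the patient as event-free.** Events after loss are missed, so the risk is understated.

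The two conventions err in opposite directions. If loss differs between arms, they also push the treatment comparison in opposite directions, so a choice made after seeing the data could move the result. Unequal loss is plausible: the trial is open-label, and the rule that stops follow-up is described for deferred-arm withdrawals only. What is at stake is the secondary endpoints at 6 and 12 months and, to a smaller extent, 30-day status after early withdrawal.

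**Working it through.** **Inputs from the Sample size section.** "The annual primary outcome event rate is 22.9" per cent, a 35% relative decrease, 240 per arm and 10% loss. The second risk is 0.65 × 22.9% = 14.885%, so the true relative risk is 0.650. The article gives no figure for the error examined here, so there is none to reproduce. (Its 240 per arm is not reproduced by a standard two-proportion calculation either: 374 per arm before loss and 416 after. That is a separate matter and nothing below depends on it.)

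**Assumptions, because the article gives neither.** Loss is non-informative and spread evenly over the year. Events follow either a constant hazard or a front-loaded curve (Weibull shape 0.3). The 22.9% belongs to the death-or-MI composite and stands in for a 12-month risk, since the article gives no risk for any single secondary endpoint.

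**Formulas.** Time runs from 0 to 1 year, with S the event-free curve, F = 1 − S, p = F(1) and L the proportion lost while event-free.
- Loss density: c = L / ∫S
- Counted event-free: R₀ = p − c(p − ∫F)
- Dropped: R₁ = R₀ / (1 − L)

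**Worked case: constant hazard, p = 0.229, L = 0.10.**
- ∫S = 0.8805, ∫F = 0.1195, c = 0.10 / 0.8805 = 0.1136
- R₀ = 0.229 − 0.1136 × (0.229 − 0.1195) = 0.2166
- R₁ = 0.2166 / 0.90 = 0.2406

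**Equal 10% loss.**

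| Event timing | True risk | Event-free | Dropped |
|---|---|---|---|
| Constant | 22.9% | 21.7% | 24.1% |
| Front-loaded | 22.9% | 22.3% | 24.8% |
| Constant | 14.9% | 14.1% | 15.7% |
| Front-loaded | 14.9% | 14.5% | 16.1% |

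The relative risk is 0.651 under either convention and either timing.

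**A third timing: 80% of events by day 30, with 10% of all patients lost whether or not they have already had an event.** Event times are taken as even within each period.
- ∫F = 0.1967
- Event-free: 0.229 − 0.10 × (0.229 − 0.1967) = 22.6%
- Unknown status at 12 months: 0.10 × (1 − 0.1967) = 8.0%
- Dropped: 22.6 / 0.920 = 24.5%
- Applied to 480 patients, about 39 have unknown status at 12 months and about 20 at 6 months.

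Over the three timings at 22.9%, dropping errs by +1.2 to +1.9 points and event-free counting by −0.3 to −1.2 points.

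**Unequal loss, true relative risk 0.650.** Ranges cover the constant and front-loaded timings.

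| Loss, immediate / deferred | Event-free | Dropped |
|---|---|---|
| 5% / 15% | 0.615 to 0.634 | 0.688 to 0.709 |
| 15% / 5% | 0.668 to 0.689 | 0.598 to 0.616 |

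**Limiting case, all loss at day 0.** Dropping gives 22.9%, with no bias. Event-free counting gives 0.90 × 22.9% = 20.6%.

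**The case against.** The strongest reply is that Table 2 defines status at fixed times, for which binary tests are valid. On this view the bias comes only from how unknown status is filled in, which an article may leave to an analysis plan that is not shown.

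Part of this stands. A reader might infer that lost patients must be either dropped or counted event-free. The article does not say so, and imputation is also compatible with these tests. It does not remove the point, because the choice of method is stated, and the stated methods cannot use partial follow-up whatever rule is added.

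Four other stronger readings are not supported:

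- **That 10% of 480, or 48 patients, are affected in every comparison.** The 10% has no time point, and a patient with an event before loss has a known status for that event. If 10% of all patients are lost evenly over the year, about 39 are unknown at 12 months and about 20 at 6 months.
- **That the roughly two-point gap between conventions passes straight into the treatment difference.** One convention would apply to both arms. Under the third timing, loss in one arm only would shift that arm by +1.6 points (24.5 − 22.9) or −0.3 points (22.6 − 22.9).
- **That a planned 12-month difference in the composite is at risk.** Table 2 sets the composite at 30 days only, and no difference is planned for any 12-month endpoint.
- **That unequal loss is likely.** The article gives no loss by arm, so unequal loss is only plausible.

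Two further objections also stand. Withdrawal before the second PCI falls early, where dropping causes little bias if loss is non-informative; but it can leave 30-day status unknown. And Kaplan–Meier estimation is itself biased if loss is related to prognosis.

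**Conclusion.** The point holds, at moderate size, for the 6- and 12-month secondary endpoints. The article commits to binary methods for them while allowing for loss and stopping follow-up for some withdrawals. At 10% equal, non-informative loss and a 22.9% risk, the absolute risk is off by up to about 2 points and the relative comparison is practically unaffected. With 5% against 15% loss, a true relative risk of 0.65 would appear as about 0.60 to 0.71, and its direction of error would depend on the convention chosen.

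These sizes rest on assumed event timing, even loss over the year, and a composite risk used in place of the single endpoints. The 30-day primary endpoint is much less exposed, though not immune. This should be changed, but it does not threaten the primary analysis.

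**What to change.** For the 6- and 12-month secondary endpoints:

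- **All-cause mortality:** Kaplan–Meier risks with a log-rank or Cox comparison.
- **Recurrent MI and unplanned target vessel revascularization:** cumulative incidence with death as the competing event.
- **Cardiac death:** cumulative incidence with non-cardiac death as the competing event.
- **For all four:** count time from randomisation, censor at last contact, and report risk differences with 95% confidence intervals.
- **Sensitivity analysis:** add one for informative loss, because censoring methods do not cure it.

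Keep the binary comparison for the 30-day primary endpoint, with a Kaplan–Meier 30-day risk difference as a check, since early withdrawals can leave that status unknown too.

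The cost is a change of wording in the analysis section and slightly more programming. Event dates and last-contact dates must be recorded on the case report form. Table 2 gives the data source only as history, so this should be confirmed.

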### Randomization

Eligible patients will be randomly assigned 1:1 to immediate stenting or deferred stenting after primary angioplasty and informed consent (Fig. 1). Random allocation sequence has been generated by using a computer-based system before recruitment started, and results are encrypted and uploaded to a network accessible to all research centers routinely in stacks of sealed electronic envelopes that can be uncovered only with passwords when patients are enrolled. The block size is 4. When a patient is eligible in one center, the investigators of that center will download and open the electronic envelope with passwords obtained from the system and get the result of random allocation and will report the information of enrollment in an online research database which will inform all of the other investigators.

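### The logistic regression adjusts for whichever baseline variables differ significantly between arms, and neither the adjusted nor the unadjusted result is named as primary

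*Protocol article*

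**What the plan says.** All of this is in the Methods of the protocol article.

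- **Covariate rule** (Statistical analyses): "Logistic regression is applied to adjust the significant variables in baseline data between the two groups". The results are to be presented as odds ratios with 95% confidence intervals. No covariate is named.
- **Threshold** (Statistical analyses): "All tests were two-tailed with a significant level of 0.05". This is the only significance level given, so it is also the natural reading of a significant baseline difference.
- **Unadjusted comparison** (Statistical analyses): "Categorical variables and outcomes were compared by using the chi-squared test or Fisher exact test". The section does not rank this test against the adjusted odds ratio.
- **Timing of baseline data** (Data collection and management): "baseline characteristics are collected with case report forms (CRFs) during hospitalization at least 24 h after PPCI". The next sentence adds that "Angiographic data are recorded in the PCI procedure".
- **Primary endpoint** (Primary endpoints): "the primary endpoint is a composite of all-cause mortality or recurrent MI at 30 days after PPCI".

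**The concern.** A significance test of a baseline difference asks whether the arms differ by more than chance. Under sound randomisation the answer is already known, so a small p-value only marks a chance imbalance. It says nothing about whether the variable predicts death or recurrent infarction. Selecting covariates this way has three consequences.

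1. The model is unknown until the allocation and the data are in, so the adjusted odds ratio is not a pre-specified quantity. Odds ratios conditional on different covariates are also not the same quantity.
2. A variable of no prognostic value can enter, which gains nothing.
3. A strong predictor that happens to be balanced stays out, although adjusting for it would improve precision.

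Two outcome analyses are listed and neither is designated as primary. If they disagree, the article does not say which one answers the trial's question.

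**Working it through.** The plan gives no figure on this point to reproduce. The checks below measure what the rule does.

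**1. How often does chance alone change the model?**

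Input from the article: level 0.05. Assumption: K independent baseline variables are tested. The chance that at least one is significant under correct randomisation is 1 − 0.95^K.

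| K | 1 − 0.95^K |
|---|---|
| 5 | 23% |
| 10 | 40% |
| 15 | 54% |
| 20 | 64% |
| 30 | 79% |

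Correlated variables would change these values.

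**2. The rule itself, simulated with several covariates**

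Inputs from the article (Sample size): 480 patients, 1:1; control risk 22.9%; 35% relative decrease. Then 0.229 × 0.65 = 0.14885, and the corresponding odds ratio is (0.14885/0.85115) / (0.229/0.771) = 0.59.

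Assumptions: 15 independent standard normal covariates, of which three are prognostic (log odds ratios 1, 0.7 and 0.7 per standard deviation); intercept −1.6; treatment odds ratio 0.59 conditional on the covariates; selection at |z| > 1.96; 6,000 trials per scenario.

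| Analysis | Rejection under no effect | Power |
|---|---|---|
| Unadjusted | 5.0% | 42.8% |
| Covariates selected by significance | 4.4% | 43.0% |
| Three prognostic covariates, pre-specified | 4.9% | 53.7% |

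At least one covariate was selected in 54% to 55% of trials, in line with step 1. Rejecting when either the unadjusted or the selected analysis was significant gave 5.6% under no effect. The simulation standard error is about 0.6 points for power, √(0.43 × 0.57/6,000), and 0.3 points for the null rates, √(0.05 × 0.95/6,000).

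Only the contrast between rows matters. Averaged over these covariates, the model implies risks of about 23.4% and 16.9%, a risk ratio of 0.72. That is weaker than the planned 0.65, so the power levels are not estimates of this trial's power.

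**3. Sensitivity with a single covariate, cardiogenic shock**

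Inputs from the article: 216 evaluable per arm (240 × 0.9), control risk 22.9%, risk ratio 0.65. Shock prevalence is 26% as cited in the Discussion, or 10% as an assumed lower value. Control-arm risk in shock is assumed; the risk without shock follows, for example (0.229 − 0.26 × 0.50)/0.74 = 13.4%. There were 40,000 trials per row. The selected analysis stratifies by shock only if shock is imbalanced at p < 0.05.

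| Prevalence | Risk in shock | Unadjusted | Selected | Always stratified |
|---|---|---|---|---|
| 26% | 40% | 57.2% | 57.4% | 58.8% |
| 26% | 50% | 57.1% | 57.4% | 62.1% |
| 26% | 60% | 57.0% | 57.7% | 66.9% |
| 10% | 40% | 56.9% | 56.9% | 57.2% |
| 10% | 50% | 57.2% | 57.3% | 58.2% |
| 10% | 60% | 57.1% | 57.1% | 59.5% |

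Under no effect, the selected rule rejected in 4.3% to 5.2% of trials. In every row it tracks the unadjusted test. The gain from always adjusting runs from under one point to about ten.

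**The case against.** The strongest defence is that the rule does little harm. It does not inflate the false-positive rate, and it loses no power against the chi-squared test that the article also names. What is lost is a gain that another analysis might bring, and that gain rests on assumed risks. It also rests on a shock prevalence cited for left main occlusion in general, whereas this trial enrols only patients who regain TIMI 3 flow and can consent. The analysts are also to be blinded to allocation, and the rule is mechanical, so it leaves less room for a deliberate choice of model. All of this stands, and it limits the size of the point. It does not rescue the rule: a mechanical rule applied blind still lets the allocation choose the covariates.

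A second defence is that covariate lists belong in the statistical analysis plan. That would answer a protocol that was silent. This one fixes a selection rule, so an analysis plan must either follow it or depart from it.

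Three stronger readings are tempting, and the article does not support them.

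- **False positives.** A reader might infer an inflated type I error rate. The simulations show the selected analysis at or slightly below 5%. Even taking whichever of two results is significant gave only 5.6%.
- **Lost early deaths.** Because the baseline forms are completed at least 24 h after PPCI, a reader might infer that patients who die on the first day drop out of the regression, or that baseline values already reflect treatment. The article gives only the time of collection. It does not say that such patients have no form, that values refer to that time, or that incomplete records are dropped. Forms can be filled in from the chart, angiographic data are recorded at the procedure, and age and first-angiogram TIMI flow are eligibility items. The unadjusted intention-to-treat comparison keeps these deaths in any case.
- **Odds ratio.** A reader might object that the design effect is a relative risk (0.65) while the result is an odds ratio (0.59 at the planned rates). The odds ratio is the natural output of logistic regression, and the proportions are reported as well. This is a reporting preference.

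**Conclusion.** The point holds as a badly fixed rule. The article lets baseline significance tests choose the adjustment set, so the adjusted odds ratio is driven by the realised allocation, and it does not say whether that result or the unadjusted test is primary. The cost is an unpredictable adjusted estimate and forgone precision.

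The logical part needs no assumption beyond correct randomisation. The sizes do. The 54% to 64% chance of a model changed by luck assumes 15 to 20 independent tests. The gap of about 11 points (53.7% − 43.0%) assumes three strong covariates. With one covariate the gain ranges from negligible to about ten points. The change should be made, but the unadjusted comparison is valid without it.

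**What to change.** 1. Delete the significance-based rule from Statistical analyses.
2. Before any unblinded look, name a short list of prognostic covariates and adjust for them whatever the observed balance. Candidates are age, cardiogenic shock or Killip class at presentation, STEMI versus NSTEMI, and TIMI flow at the first angiogram.
3. State whether the unadjusted or the adjusted analysis is primary; the other becomes supportive.
4. As a minor clarification in Data collection and management, say that these covariates are recorded as values at or before randomisation for every randomised patient, including those who die within 24 h.

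The cost is a few sentences in the protocol and analysis plan and one instruction for the case report form. Sample size and treatment are unaffected.

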## Methods

### Objectives and study design

The aim of this open-label, multicenter RCT is to compare immediate stenting with deferred stenting for LM-AMI in 30 hospitals in China. We hypothesize that patients with LM-AMI receiving deferred stent implantation will have improved short-term and long-term clinical outcomes compared with those receiving immediate stenting. A total of 480 patients with diagnosed LM-AMI will be randomly assigned in a 1:1 ratio to either deferred stenting or immediate stenting and followed for up to 12 months.

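### The trial is planned on a risk ratio of 0.65, but the only effect estimate named with an interval is an odds ratio, adjusted for covariates chosen by baseline significance

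*Protocol article*

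**What the plan says.** The Sample size section of the Protocol article sets the target effect as a proportional reduction in the outcome: "we determined a 35% relative decrease in primary outcome". The starting rate is 22.9%, and the article labels it annual: "The annual primary outcome event rate is 22.9" per cent. The error rates are tied to that same reduction: "two-sided alpha of 0.05 and 80% power to demonstrate the relative decrease".

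Under Primary endpoints the outcome is binary and short-term: "the primary endpoint is a composite of all-cause mortality or recurrent MI at 30 days after PPCI".

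The Statistical analyses section does three things with binary outcomes:

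- It describes categorical data as proportions and percentages.
- It tests them: "Categorical variables and outcomes were compared by using the chi-squared test or Fisher exact test".
- It fits a logistic regression, adjusted for baseline variables found to differ significantly between the arms, to "assess the outcomes presented with odds ratios and 95% confidence intervals".

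No risk ratio or risk difference with a confidence interval is named.

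**The concern.** The planning hypothesis and the reported estimate are on different scales. A reader who sees the odds ratio beside the planned 35% reduction will be inclined to compare the two directly. When events are not rare, the odds ratio lies further from 1 than the risk ratio for the same pair of risks, so the comparison flatters the treatment.

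The covariate rule adds a second difficulty. The odds ratio is non-collapsible: adjusting for a prognostic variable changes its value even when that variable is balanced and nothing is confounded. Here the adjustment set is whatever happens to differ significantly at baseline. In a randomised trial such differences arise by chance. Two runs of the same trial with the same true effect could therefore adjust for different variables and estimate different quantities. At stake is how the main estimate is read and whether its definition is fixed in advance. The validity of the test is not at stake.

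**Working it through.** **Inputs (all from the Protocol article)**

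- Control rate p1 = 0.229 and a 35% relative decrease (Sample size).
- Two-sided alpha 0.05, power 80%, 240 per arm including 10% loss (Sample size: "The study planned to enroll 240 patients for each arm given a 10% rate of loss").
- 1:1 allocation (Objectives and study design).
- Assumption: the 30-day control risk is not given, so a range of 5% to 30% is shown.

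**Step 1. Reproduce the plan's own figure.** With p2 = 0.65 × 0.229 = 0.14885 and mean risk 0.188925:

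n = [1.960 × √(2 × 0.188925 × 0.811075) + 0.842 × √(0.229 × 0.771 + 0.14885 × 0.85115)]² / (0.08015)² ≈ 374 per arm, and 374 / 0.90 ≈ 416 after loss.

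This does not give 240. Continuity-corrected, unpooled, arcsine, one-sided and log-rank variants do not give it either. Reading the 35% as a reduction in odds moves further away: p2 = 0.1618 and 546 per arm, or 607 after loss. The stated sample size therefore cannot show that an odds ratio was meant. The plain reading, a reduction in risk, stands. The shortfall in the sample size is a separate matter and is not part of this point.

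**Step 2. Convert the planned risk ratio to an odds ratio.**

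OR = [p2 / (1 − p2)] / [p1 / (1 − p1)]

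At the stated rate: (0.14885 / 0.85115) / (0.229 / 0.771) = 0.1749 / 0.2970 = 0.589.

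A 35% reduction in risk is thus a 41% reduction in odds.

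**Step 3. Vary the control risk, keeping the risk ratio at 0.65.**

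| Control risk | Deferred-arm risk | Risk difference (points) | Odds ratio |
|---|---|---|---|
| 5% (assumed) | 3.25% | 1.75 | 0.638 |
| 10% (assumed) | 6.5% | 3.5 | 0.626 |
| 15% (assumed) | 9.75% | 5.25 | 0.612 |
| 20% (assumed) | 13.0% | 7.0 | 0.598 |
| 22.9% (stated, annual) | 14.9% | 8.0 | 0.589 |
| 30% (assumed) | 19.5% | 10.5 | 0.565 |

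**Step 4. The reverse reading.** Suppose the trial reports an odds ratio of 0.65 with a control risk of 22.9%. Odds in the deferred arm = 0.65 × 0.2970 = 0.1931. Risk = 0.1931 / 1.1931 = 0.162. Risk ratio = 0.162 / 0.229 = 0.71. A result that looks like the planned effect would be a 29% reduction in risk, short of 35%.

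**Step 5. What the scale does not touch.** The chi-squared and Fisher tests address equality of two proportions. Their null hypothesis is the same whether the effect is expressed as a risk ratio, an odds ratio or a difference. Type I error, power and the required number of patients do not change with the measure reported.

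**The case against.** The strongest defence is that nothing is stated wrongly. The planned test matches the planning assumption of two proportions, and an odds ratio is a legitimate summary on its own scale. Percentages are to be described, so a reader can form the crude risk ratio and set it beside 0.65. The article is also a condensed account, and the analysis plan, which is not shown, may name further measures.

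Most of this stands, and it rules out several stronger readings that a reader might infer:

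- *The odds ratio overstates the benefit.* It does so only if it is read as a risk ratio.
- *The result cannot be compared with the planned effect.* It can, crudely, from the percentages. What the article does not commit to is an interval for that comparison, and the crude figure need not agree with the adjusted one.
- *Readers will see 41% instead of 35%.* That size rests on 22.9%, which the article calls annual, while the endpoint is at 30 days. At an assumed 30-day risk of 5–10% the odds ratio is 0.63–0.64, close to 0.65.
- *Adjustment for cardiogenic shock would push the odds ratio to about 0.50–0.57.* Such figures need assumed event risks in shock (40–60%). The 26% prevalence in the Discussion is a cited background figure and does not describe the enrolled patients, who must reach TIMI 3 flow. The plan does not name shock as a covariate. The documents support no particular size for this effect.

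A conditional odds ratio that differs from the marginal one is also a different estimand, not a biased one. What remains is that the article does state how covariates are chosen, and that rule leaves the estimand undefined until the baseline data are seen. This is a stated choice and cannot be put down to detail left to the analysis plan.

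**Conclusion.** The point holds as a modest mismatch in reporting. The trial is planned on a risk ratio of 0.65, and the one estimate named with an interval is an adjusted odds ratio. The two differ by 0.06 at a control risk of 22.9% (0.59 against 0.65) and by 0.01 to 0.02 at an assumed 30-day risk of 5–10%. Which size applies to the primary endpoint cannot be settled, because the article gives no 30-day rate. The dependence of the adjusted estimate on chance imbalance follows from the stated covariate rule together with non-collapsibility, and its size cannot be derived from the article. The conclusion assumes that the 35% is a reduction in risk, which is its plain meaning. It implies no error in the test, in type I error or in power.

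**What to change.** In the Statistical analyses section, or in the analysis plan:

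1. Name the risk ratio and the risk difference, each with a 95% confidence interval, as the main effect measures for the primary and secondary binary outcomes. Keep the chi-squared or Fisher test as it is.
2. For any adjusted analysis, drop selection by baseline significance. List a small set of baseline covariates in advance, chosen because they are expected to predict the outcome.
3. Obtain the adjusted risk ratio and risk difference by marginal standardisation after the logistic model. A modified Poisson model with robust standard errors is an alternative for the risk ratio.
4. Keep the odds ratio as a supportive result, labelled as such.

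The cost is a few sentences of wording and a few lines of Stata or SAS code, both of which the article already names. Sample size does not change, and data collection does not change as long as the covariates are taken from the baseline data already collected. The covariate list should be fixed before outcome data by arm are seen.
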